### Exit criteria

Patients will be withdrawn from the study if parents make specific request for the treatment to be discontinued before 72 hours, in case of severe bleeding, thrombosis, or pulmonary hypertension difficult to treat, arrhythmia, clinical electroencephalographic or neuroimaging evidence of irreversible severe brain damage.

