### Objectives

#### Major objectives: safety and efficacy of TPM associated with moderate whole-body hypothermia

The first purpose of this study is to confirm the safety of TPM administration in asphyxiated newborns. For this purpose, cardiac and respiratory parameters (heart frequency, blood pressure, oxygen saturation, respiratory support), will be continuously monitored. Blood samplings will be performed to check renal, liver and metabolic balance.

TPM is considered to be safe and generally well tolerated in children. The safety profile of TPM might be different in neonates with HIE treated with hypothermia than in adults receiving chronic therapy for epilepsy. TPM can cause metabolic acidosis, especially in pediatric patients, because of carbonic anhydrase inhibition at proximal renal tubule with consequent renal loss of bicarbonate
[106,107]. In as many as 48% of adults and 67% of children with epilepsy treated with TPM, a variable degree of metabolic acidosis develops. However, in most reported cases, bicarbonate levels did not decrease to be clinically significant. Only 11% of patients had serum bicarbonate levels <17 mEq/L
[106,108] and symptomatic cases were successfully treated with sodium bicarbonate supplementation
[106]. Although this observation is reassuring, metabolic acidosis is usually severe in neonates with HIE, who have metabolic acidosis because of both asphyxia and renal impairment. In infants, metabolic acidosis usually occurs after 8 to 26 days of TPM treatment, with dosages as high as 8.2 to 26 mg/kg/day
[109]. Similar to other carbonic acid anhydrase inhibitors, long-course TPM therapy is associated with increased risk of nephrolithiasis in adults
[106,107]. Angle closure glaucoma and acute myopia are additional, though potentially reversible, adverse events related to TPM treatment in the pediatric age
[106,107,110]. In a safety study, we found no signs of metabolic acidosis in newborns co-treated with moderate hypothermia and TPM; abdomen ultrasound scanning did not show kidney stones and ophthalmological evaluation was normal in all treated newborns
[104].

The second objective of this study is to evaluate the efficacy of TPM add-on therapy, evaluating the clinical outcome of enrolled newborns. The neurological and neuroradiologic outcome of newborns treated with hypothermia plus TPM will be compared to the outcome of control group that received hypothermia alone.

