### Experimental plan and data analysis

Based on the medical literature, the mean incidence of the combined frequency of mortality and severe neurodevelopmental disability in survivors at 18 months of age is approximately 50%. In fact this percentage is 55% in the cool Cap study
[66], 44% in the NICHD study
[68], 45% in the TOBY trial
[69], 51.4% in the ICE trial
[70], and 50.9% in the neo.nEURO.network study
[71]. We hypothesize that treatment with TPM may reduce the incidence of the combined frequency of mortality and severe neurodevelopmental disability in survivors at 18 months at 15%. In order to compare the incidence of this primary outcome between newborns receiving TPM plus hypothermia (treated) and those only receiving hypothermia (control group), the estimated sample size was calculated, considering normal distribution, an alpha error of 0.05 and a power of 80 percent. The sample size for each group is 32 participants.

The three units have an overall admission rate of approximately 10 term newborns with HIE per year. Due to the high hypothetical advantages of this treatment, we estimate 90-100% rate of consent and we predict we would recruit the 64 newborns over around 24 months period with a realistic safety margin.

Mortality, the incidence of severe neuromotor disability, cortical vision, sensorineural hearing loss, developmental delay, epilepsy will be evaluated at 18 months of life.

To evaluate TPM safety, cardiac and respiratory parameters (heart frequency, blood pressure, oxygen saturation, respiratory support), will be continuously monitored. Blood samplings will be performed to check renal, liver and metabolic balance. Kruskal-Wallis test will be used to assess possible differences between newborns treated or not with TPM. The safety will be also evaluated by means of relative risk (RR)
[132]. RR will be calculated as the ratio between the probabilities of side effects in the TPM group with respect to the control group. Values of RR lower than 1, will be associated to the efficacy of the treatment.

Finally, we will evaluate the different distribution of any brain lesions on MRI brain highlighted.The RR is calculated for each item studied. An RR <1 indicates an improvement of neurological, neurodevelopmental and neuroradiologic hypothermia due to the association-topiramate.

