### Primary outcome

The neurological and neuroimaging outcome of these two groups of infants will be compared to determine whether adjunctive treatment with TPM improves the neuroprotective effect of hypothermic treatment.

The primary outcome will be the combined frequency of mortality and severe neurodevelopmental disability in survivors at 24 months of age. Severe disability is defined as Bayley III
[123] cognitive development index 3 SDs below mean or any one of the components of severe sensorimotor disability (e.g. inability to walk, sit, feed using hands, communicate (Bayley III language development index 3 SDs below mean), hear (80 dB sensory neural hearing loss) or see.

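### The exit criteria take infants out of the study, not only off treatment, on a trigger close to the primary outcome, and conflict with follow-up of every newborn to 24 months

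*Protocol article*

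**What the plan says.** The protocol article's Exit criteria section is a single sentence. It opens "Patients will be withdrawn from the study if parents make specific request for the treatment to be discontinued before 72 hours", continues "in case of severe bleeding, thrombosis, or pulmonary hypertension difficult to treat, arrhythmia", and ends with "clinical electroencephalographic or neuroimaging evidence of irreversible severe brain damage". The sentence uses both words, treatment and study, and makes stopping the first a reason for leaving the second. The 72-hour limit is attached to the parental request; no time limit is given for the other triggers.

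Under Primary outcome: "The primary outcome will be the combined frequency of mortality and severe neurodevelopmental disability in survivors at 24 months of age".

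Under Major objectives: "The first purpose of this study is to confirm the safety of TPM administration in asphyxiated newborns". Experimental plan and data analysis gives the safety measure: "RR will be calculated as the ratio between the probabilities of side effects in the TPM group with respect to the control group".

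Neurological follow-up says that every newborn is seen at 1, 3, 6, 12, 18 and 24 months. It does not mention infants who have met an exit criterion. That section and Neuroradiologic follow-up state that the follow-up neurologists and neuroradiologists are blinded to topiramate.

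**The concern.** An infant with irreversible severe brain damage on EEG or imaging is among those most likely to die or be severely disabled. A rule that removes this infant from the study selects on an early form of the primary outcome, after randomisation. If the 24-month status is then never collected, an as-randomised analysis cannot recover it.

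Two things would be at stake. If exits are equally common among failing infants in both arms, events are lost and power falls. If they differ by arm, the comparison itself is biased. Differential exit is plausible: no placebo is described, topiramate goes in by orogastric tube, so bedside staff probably know the arm, and several triggers need judgement about what is severe, difficult to treat or irreversible.

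For safety, an infant who leaves after one severe event contributes no later events, including any that would count towards multiorgan dysfunction, a secondary outcome defined as adverse events in three or more organ systems.

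**Working it through.** **Does the rule mainly stop treatment?** The Topiramate section gives three doses over the first three days. Neuroradiologic follow-up schedules MRI at the end of cooling within the first week, then at three and 18 months. By then the topiramate course is ending or over. On this schedule the imaging trigger can do little except remove the infant from the study.

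**The plan's own sample size.** Inputs from Experimental plan and data analysis: control rate 50% ("severe neurodevelopmental disability in survivors at 18 months of age is approximately 50" percent), topiramate rate 15%, alpha 0.05 (two-sided assumed), power 80%, 32 per group.

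n = [1.96·√(2p̄(1−p̄)) + 0.842·√(p₁(1−p₁)+p₂(1−p₂))]² / (p₁−p₂)², with p̄ = 0.325

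= [1.96·√0.43875 + 0.842·√0.3775]² / 0.35² = 26.9, so 27 per arm. With continuity correction it is 33. Fisher exact power is 79.7% at 31 per arm and 81.5% at 32. The stated 32 is therefore reproduced. Total recruitment is 2 × 32 = 64, so the article describes no allowance for exits.

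**Effect of withdrawal on the observed rates.** Let f be the fraction of failing infants (death or severe disability) who are withdrawn and not counted, with all other infants retained. The documents give no value of f; every value below is an assumption. In an arm with true rate p:

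observed rate = p(1−f)/(1−pf), expected number left = 32(1−pf)

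For p = 0.50:
- f = 20%: 0.40/0.90 = 44.4%, 28.8 infants left
- f = 40%: 0.30/0.80 = 37.5%, 25.6 infants left

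**No true effect (50% in both arms).** Simulated trials, 32 per arm, uncorrected pooled z-test at 1.96 on the infants who remain:

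| Failures withdrawn, TPM / control | Expected observed rates, TPM / control | Significant in favour of TPM |
|---|---|---|
| 0% / 0% | 50.0% / 50.0% | 3.0% |
| 20% / 20% | 44.4% / 44.4% | about 2.6% |
| 40% / 40% | 37.5% / 37.5% | about 2.6% |
| 40% / 20% | 37.5% / 44.4% | about 7.6% |
| 40% / 0% | 37.5% / 50.0% | 15.7% |
| 20% / 40% | 44.4% / 37.5% | 0.7% |

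The first row exceeds the nominal 2.5% because the test is discrete at this sample size.

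**Planned effect (50% vs 15%), equal withdrawal in both arms, same test:**

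| Failures withdrawn | Observed rates, control / TPM | Risk difference | Power |
|---|---|---|---|
| 0% | 50.0% / 15.0% | 35.0 points | about 87% |
| 10% | 47.4% / 13.7% | 33.7 points | 85% |
| 20% | 44.4% / 12.4% | 32.1 points | 82% |
| 40% | 37.5% / 9.6% | 27.9 points | 73% |

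The normal-approximation formula gives slightly lower values for the first three rows (86.6%, 83.8%, 80.3%) and the same pattern. On the Fisher scale the starting point is 81.5%, so only 1.5 points separate the design from its 80% target before any infant is lost.

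**The case against.** Several stronger readings are tempting, and the article does not support them.

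- **That the triggering safety events drop out of the relative risk.** Bleeding, thrombosis, pulmonary hypertension or arrhythmia must occur before it can cause exit, and it would occur under the monitoring scheduled through cooling and after re-warming. The article does not say that data collected before exit are discarded. What is at risk is later safety events and the long-term outcome.
- **That exited infants are excluded from the analysis.** The article has a withdrawal rule, not an analysis exclusion. The analysis set may be defined in a statistical analysis plan that is not shown. The calculations above assume a complete-case analysis. This limits the claim about bias but does not remove the problem, because an analysis set cannot supply outcomes that were not collected.
- **That unblinded staff decide every exit.** The section names no decision-maker. The neuroradiologists responsible for follow-up are blinded, and their MRI starts in the first week, so the imaging trigger may well be judged blind. Bedside knowledge of the arm is likely but inferred.
- **That the bias favours topiramate.** Equal withdrawal gives no inflation, and more withdrawal on control works against topiramate.

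The best counter-evidence is the Neurological follow-up section, which evaluates every newborn to 24 months. It may mean that exited infants are still followed. But it reads as the general schedule, says nothing about them, and cannot be squared with an instruction to withdraw patients from the study. The conflict stands.

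**Conclusion.** The point holds as a defect in a stated rule, not as a missing detail. Followed as written, the Exit criteria would selectively lose the 18/24-month outcome of infants likely to be primary events, together with their later safety events, and they contradict the follow-up of every newborn.

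Confidence is high for the wording and the conflict. It is low for size and direction, which rest on assumed exit shares and a complete-case analysis. Over the shares examined, false significance in favour of topiramate runs from 0.7% to 15.7%, against 3.0% with no withdrawal. Power on the uncorrected test stays above 80% when 10% or 20% of failures are withdrawn equally and falls to 73% at 40%. It should be corrected because, in a trial of 64 infants, outcomes lost this way cannot be recovered afterwards.

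**What to change.** Reconcile Exit criteria, Neurological follow-up and Primary outcome by separating two things: leaving study treatment and leaving follow-up.

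- State that every randomised infant is followed to the primary visit, whatever happens to treatment, unless the parents withdraw consent to follow-up itself. A request to stop treatment is not such a withdrawal.
- Analyse all infants in the arm assigned, counting death or severe disability after a treatment stop as a primary event.
- Keep all adverse events, before and after any treatment stop, in the safety comparison.
- Report the number of infants meeting each exit criterion by arm.

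The amendment must also name one primary visit, since Primary outcome says 24 months and Experimental plan and data analysis says 18. Which events should affect treatment, and which treatment, is left to the clinical team.

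The cost is a wording amendment. The visits needed are already in the general follow-up schedule, and no change to the sample size is required by this point alone.

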### Measurement of outcomes

#### Primary endpoint

To evaluate if the TPM administration reduces the cerebral damage of newborns with HIE and treated with therapeutic hypothermia, neurological and neuroradiologic follow-up are planned at different stages.

#### Secondary endpoint

a. To evaluate the safety of TPM treatment, cardiac and respiratory parameters (heart frequency, blood pressure, oxygen saturation, respiratory support) will be continuously monitored; blood samplings will be performed to check renal, liver and metabolic balance

b. To evaluate if TPM improves the functional and structural outcome, visual function is planned at 40 weeks gestational age, 4 ½, 12, 18 and 24 months corrected age.

#### Confidentiality

The participants’ data collected during this trial will be kept confidential. Study staff will have access to the data as well as the participants’ medical records as they pertain to this study. Published results will not contain any information that would identify individual participants.

## Discussion

The objective of this research is highly ambitious: to find a treatment procedure that is simple, inexpensive, well tolerated and with few adverse effects, able to reduce post-ischemic neuronal damage. Neuroprotection is a major health care priority, given the enormous burden of human suffering and financial cost caused by perinatal brain damage. Hypothermic treatment is recognized as a neuroprotective treatment after a profound neonatal insult. However, it is clear from previously published clinical trials and animal studies that hypothermia alone does not provide complete protection. Neuroprotective drugs added during or after hypothermia might improve neurologic protection, by extending the therapeutic window or providing long-lasting additive or synergistic action
[133]. This combination treatment could open new perspectives for the management of asphyxiated infants. To date, no clinical study has evaluated the efficacy of the combined treatment hypothermia and TPM, an antiglutaminergic drug mainly used for the treatment of epilepsy. On the other hand, it is important to consider that drugs administered during the neonatal period may be dangerous to the immature brain, and hypothermia can modify their pharmacokinetics. In fact, excretion of many drugs and their metabolites can be modified by hypothermia; failure of liver and kidney clearance due to hypoxic-ischemic injury could exacerbate any toxicity. In newborns with HIE, TPM pharmacokinetic properties appear to be modified by concomitant hypothermia, but the dosage of 5 mg/kg appears safe. In this study the dosage will be increased to 10 mg/kg, likewise in other studies. For this reason one of the main objectives of this study is to confirm the safety of TPM added to hypothermia.

## Abbreviations

HIE: Hypoxic ischemic encephalopathy; EEG: Electroencephalography; AMPA: Alpha-amino-3-hydroxy-5-methyl-4-isoxazolepropionate; NMDA: *N*-methyl-D-aspartate; TPM: Topiramate; MRI: Magnetic Resonance Imaging; DTI: Diffusion tensor imaging.
